[figure not shown]

# 1 Background

Pandemic influenza A viruses have caused significant morbidity and mortality during the last century (1). In April 2009 a new influenza A virus started to circulate in North America causing upper respiratory tract infections. Initially, in Mexico the mortality to this virus appeared to be relatively high (ca. 2%), but based on wide-spread diagnostic activity in all countries around the world the disease resembles more a severe seasonal influenza A virus infection. Molecular characterization of the virus by the scientists at U.S. Centers for Disease Control and Prevention (CDC) revealed that the circulating virus was a previously unrecognised strain of subtype H1N1 influenza A virus in which two polymerase genes (PA and PB2) were originating from North American avian influenza A viruses, one polymerase gene (PB1) from human seasonal influenza A virus and three genes from North American (hemagglutinin, nucleoprotein, NS protein) and two genes (neuraminidase, M protein) from Eurasian swine influenza A viruses (2). The virus likely developed in swine from a triple reassortant swine influenza A virus that has been circulating in North America (3) and another swine virus that simultaneously infected pigs. The new influenza A/H1N1 swine-lineage (swl) virus is genetically and antigenically different from past human seasonal influenza A viruses. There is approximately only 79% and 81% amino acid identity between the new A(H1N1)v (California strains) and H1N1 vaccine (Brisbane strain; H1N1 component of the 2009/2010 seasonal influenza vaccine) virus hemagglutinin and neuraminidase genes, respectively. It is thus expected that humans do not have significant pre-existing immunity against the new virus making virtually the whole world population susceptible for the disease. Rapid identification of the new influenza A(H1N1)v virus and the availability of many seed virus stocks for vaccine manufacturers has enabled a rapid development and production of vaccines against the new influenza A(H1N1)v virus. First vaccines are ready for clinical testing and many European governments have made an advance purchase agreement to buy A(H1N1)v vaccines either for the whole population or for defined priority groups for vaccination.

Finland has made an agreement to buy one dose of A(H1N1)v vaccine for the whole population and negotiates of a second dose. The likely availability of the first doses of the vaccine will enable the vaccination of at least some parts of population during the

last months of the year 2009. The decision of the vaccination strategy will be done, when enough knowledge is available of the epidemiological and clinical features of the disease. If mass vaccinations will start with a new vaccine, which can not be evaluated as thoroughly as other new vaccines, it is essential to have a plan in place to get information of the immunogenicity, safety and clinical effectiveness of the vaccine as rapidly as possible.

## **2 Objectives**

### **2.1 Primary objective**

- To determine the effectiveness of an A(H1N1)v influenza vaccination in preventing the first episode of laboratory-confirmed infection with the novel, pandemic influenza A(H1N1)v virus among community-dwelling and recently vaccinated adults as compared to unvaccinated adults from a cohort of at least 4,000 persons

### **2.2 Secondary objectives**

- To assess the safety for 6 months after vaccination with the A(H1N1)v vaccine during the follow up;
- To determine humoral and cellular immune responses to one or two doses of the A(H1N1)v vaccine in 200 adults aged 18 to 75 years
- To evaluate the incidence, severity and possible complications of laboratory-confirmed infection with the novel A(H1N1)v influenza virus;
- To explore the effectiveness of the A(H1N1)v vaccine in subgroups stratified by age

## **3 Study design**

In case that the government recommends vaccination with pandemic A(H1N1)v vaccine, it is no longer ethical to conduct randomized trials. Therefore, a prospective observational cohort study is the most reasonable alternative in which the incidence rates of A(H1N1)v disease in exposed (i.e. vaccinated) and unexposed (i.e. unvaccinated) adults are compared (the total study cohort). This cohort design also allows assessment of the immunogenicity of the A(H1N1)v vaccine among a subgroup

of vaccinated adults (the immunogenicity cohort). Collaboration will be established with the public health care settings providing primary, secondary and tertiary health care to persons in the study cohort for follow-up of the safety of the vaccination and severity of the A(H1N1)v influenza cases. In addition, existing medical registers will be used to follow-up of the safety and severity outcomes. In order to address the study objectives in the most optimal way, a flexible approach to study design, target group of enrollment, and the length of follow-up is required, so that changes can be made in response to accumulating information. Since no vaccine intervention is offered in the frame of this study, study enrollment procedure need to follow closely the vaccine delivery schedules, mass vaccination recommendations, as well as vaccine uptake among those who will be offered the vaccine as part of the national vaccination campaign. In addition, uncertainty regarding the peak of epidemics provide further complications, which necessitates the possibility for rapid re-evaluation of the study cohort enrollment plans and the length of follow-up, as is customary in these types of observational studies. According to the current available information, the study period of data collection is envisaged from September-October 2009 until the first wave of A(H1N1)v influenza is considered to be over in the region, presumably by the end of April 2010.

## **4 Study population**

The subjects will be enrolled from the population assigned to use the services of Tampere health centre.

### **4.1 Eligibility criteria**

#### **4.1.1 Inclusion criteria**

- Full legal competence;
- Written informed consent obtained;
- Assigned to use the services of Tampere health centre and community-dwelling;
- At least 18 and no more than 75 years old, inclusive;
- Belongs to the target group of A(H1N1)v vaccination in the region during the pandemic vaccination campaign;

- Able to communicate fluently in Finnish or Swedish
- Able to adhere to all protocol required study procedures without any special burden or risk, as judged by the investigator or designate.

#### **4.1.2 Exclusion criteria**

- For the total study cohort, no specific exclusion criteria will be applied;
- For the subgroup for follow-up of immunogenicity of the vaccine (immunogenicity cohort), exclusion criteria comprise:
  - previous severe allergic reaction to influenza vaccines or known severe allergy to the ingredients of the vaccine
  - previous severe allergic reaction to eggs
  - significant immunological disorder

Participation in the study will be offered to subjects defined by the inclusion and exclusion criteria, until 4,000 subjects have been enrolled. A random sample is preferred, but the sample may be weighted by taking into account the prioritisation of the national A(H1N1)v vaccination campaign and/or vaccine uptake. Participation in the immunogenicity cohort will be offered to participants of the total study cohort who intend to take the A(H1N1)v vaccine during the vaccination campaign according to the national recommendations. In total, 200 individuals will be recruited for blood sampling and follow-up of immunogenicity and safety of the vaccine.

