## **8.2 Assessment of immunogenicity**

From the subgroup of the 200 persons participating in the cohort for assessing the immunogenicity of the A(H1N1)v vaccine, 60 ml of venous blood will be drawn at the day of (and before) the first vaccination. At a visit scheduled at 4 weeks after vaccination, 60 ml of venous blood will be drawn for assessment of humoral and cellular immunity. Immunogenicity will be assessed as the fold-increase between pre- and post-vaccination immune responses. If the national vaccination strategy will include two doses of A(H1N1)v vaccine, similar pre-vaccination blood sample (60 ml) will be drawn at the day of the second vaccination and a post-vaccination blood sample (60 ml) will be obtained 4 weeks after the second vaccination, for assessing the humoral and cellular immune reaction to the second vaccine dose. A blood sample (60 ml) for assessing the long term immunity level is scheduled to be obtained 6 months after the administration of the last vaccine dose.

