each year. Influenza A virus-specific RT-PCR is based on general identification of influenza A viruses by matrix (M1) gene-specific primers that identify all influenza A viruses independent of their H or N gene subtype. Virus Infection Unit has also developed swine-origin pandemic influenza A(H1N1)v specific RT-PCR assay based on H1 and NS1 gene specific primers that reliably enable the detection of swine-origin A(H1N1)v virus infections. The assay was successfully used to determine the first influenza A(H1N1)v infection cases in Finland in early May, 2009. Thus the methodology for the rapid and specific influenza A virus diagnostics, for isolation and further characterization of influenza viruses are well established in the laboratory.

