### **11.3 Statistical methods for analyses**

The incidence of the laboratory-confirmed H1N1 pandemic influenza will be calculated as the number of cases divided by the person-time at risk, where person-time at risk is defined as compliance to the regular contacts. Periodic variation of incidence in calendar time will also be explored both in vaccinated and unvaccinated groups. Event-history analysis methods will be used for the evaluation of the effectiveness of the vaccine, where the risk of acquiring A(H1N1)v-influenza will be compared between the vaccinated/unvaccinated states, by accounting for calendar time and other potential confounders. Vaccine effectiveness will be calculated as 1- relative risk. For the vaccine adverse events, case-series method will be used for comparing the incidences between risk and non-risk periods. Descriptive analysis will be conducted for the immunogenicity cohort, such as calculation of geometric mean titres and percentages over pre-defined thresholds. Due to the nature of the study (see Section 3), other descriptive analyses and tests of hypotheses may also be carried out but the choice of subsequent hypotheses will be data dependent

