## 15 Time schedule of the study

The enrolment is estimated to start when the epidemic is considered to have started in the region or when the government has decided to start vaccination against A(H1N1)v influenza. The study period for follow-up of occurrence of laboratory-confirmed A(H1N1)v influenza cases is envisioned from September-October 2009 until the first wave of A(H1N1)v influenza is considered to be over in the region, and 30 April 2010 at latest. The study period for collecting immunogenicity data depends on availability of vaccines and will last until 6-7 months have elapsed since the last vaccination of the participants of the immunogenicity study. The follow-up of safety and severity outcome events from registers will last up to 6 months after the end of the clinical follow up. If relevant reasons arise during the pandemic, the consent allows a long term follow up with registers up to 3 years after the start of the study. The consent will also include permission to follow up the health of children born to women who are pregnant during the follow up until the child is one year old. The laboratory analyses and statistical analysis are phased from April 2010 until the end of 2010.

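### Time at risk takes no account of A(H1N1)v infection before entry, so people already infected are counted as at risk for a first episode

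*Protocol*

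**What the plan says.** **Effectiveness**
- Protocol 2.1 sets the endpoint as the "first episode of laboratory-confirmed infection with the novel, pandemic influenza A(H1N1)v virus".
- Protocol 4.1.2 on eligibility: "For the total study cohort, no specific exclusion criteria will be applied".
- Protocol 15 on timing: "The enrolment is estimated to start when the epidemic is considered to have started in the region", or when the government decides to vaccinate. Follow-up is envisaged from September-October 2009. Protocol 10.2.1 dates the virus in the country earlier: "The assay was successfully used to determine the first influenza A(H1N1)v infection cases in Finland in early May, 2009".
- Protocol 7.1 lists the baseline items: personal and work background, illnesses, drugs, vaccinations and pregnancy. Earlier influenza-like illness (ILI) or A(H1N1)v is not named. Blood is drawn in the total cohort only when ILI occurs (8.1).
- Protocol 11.3 computes incidence over person-time, "where person-time at risk is defined as compliance to the regular contacts". It adds that the comparison will account for calendar time and other possible confounders.
- Protocol 8.1 stops ILI follow-up after a first confirmed case. Protocol 8.1.1 collects positive test results from local laboratory databases and the Communicable Disease Register in order to find missed cases.

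**Immunogenicity**
- Protocol 8.2: "Immunogenicity will be assessed as the fold-increase between pre- and post-vaccination immune responses". Samples are taken before dose 1 on the same day, at 4 weeks, and 6 months after the last dose, with an extra pair if a second dose is given. Protocol 11.3 summarises them as geometric mean titres (GMT) and percentages above thresholds. Neither section has a rule for infection between samples.

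**The concern.** A confirmed infection ends time at risk if it happens after entry, but has no consequence if it happened before. On the protocol's own dates, infection before entry is possible: the virus was in the country from May 2009, enrolment may open in an epidemic already under way, and it continues until 4,000 people have joined.

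Someone who has had A(H1N1)v cannot contribute a first episode, yet would add person-time. The comparator is small, about 400 of 4,000, so a few dozen such people there change its incidence noticeably. The success criterion in 11.2 is a lower 95% limit for VE above 50%, so a modest shift in VE can decide the result. A later analysis plan could define a risk-set rule from register data, but it could not adjust for self-reported history that nobody collected.

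In the 200-person cohort the related worry is that a titre rise caused by infection is read as vaccine response or persistence. Section 5.2 guards against the mirror problem: it uses paired antibody titres as supporting evidence in vaccinated people only if 4 weeks have passed since the last dose.

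**Working it through.** **1. The plan's own figure.** Inputs from 11.2: 4,000 people, 90% uptake, 20% attack rate in the unvaccinated, VE 70%, lower 95% limit above 50%, power 95%.
- Unvaccinated: 400 × 0.20 = 80 cases. Vaccinated: risk 0.20 × 0.30 = 0.06, and 3,600 × 0.06 = 216 cases.
- Linear contrast: (0.5 × 0.20 − 0.06) / √(0.06 × 0.94/3,600 + 0.25 × 0.20 × 0.80/400) = 0.04/0.01075 = 3.72. Power = Φ(3.72 − 1.96) = 96.1%.
- Poisson log rate ratio: ln(0.5/0.3)/√(1/80 + 1/216) = 0.511/0.131 = 3.90. Power = Φ(3.90 − 1.96) = 97.4%.

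The stated 95% is reproduced closely enough and is not in error. It treats everyone as susceptible at entry.

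**2. Effect of earlier infection on VE.** Let u and v be the shares already immune among the unvaccinated and vaccinated. The documents give neither, so the values below are assumptions. Earlier infection is taken as fully protective, and VE is 70% in everyone else.

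Observed VE = 1 − [0.06 × (1 − v)] / [0.20 × (1 − u)]

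Power = Φ( ln(0.5/(1 − VE)) / √(1/[80(1 − u)] + 1/[216(1 − v)]) − 1.96 )

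| u | v | Cases, unvaccinated | Cases, vaccinated | Observed VE | Power (Poisson) |
|---|---|---|---|---|---|
| 0% | 0% | 80 | 216 | 70.0% | 97.4% |
| 5% | 5% | 76 | 205.2 | 70.0% | 96.7% |
| 20% | 20% | 64 | 172.8 | 70.0% | 93.7% |
| 10% | 5% | 72 | 205.2 | 68.3% | 91.5% |
| 20% | 5% | 64 | 205.2 | 64.4% | 65.8% |
| 5% | 10% | 76 | 194.4 | 71.6% | 98.7% |
| 5% | 20% | 76 | 172.8 | 74.7% | 99.9% |

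Equal shares leave VE unchanged and cost little power. Unequal shares bias VE either way. The higher power in the last two rows reflects an overstated VE and is no gain. These rows show the mechanism and are not forecasts: 20%/5% means 80 + 180 = 260 people already infected (6.5% of the cohort), and 5%/20% means 20 + 720 = 740 (18.5%), close to the 20% the plan assumes for the unvaccinated over the whole wave.

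**3. Immunogenicity.** Infection before entry is already in the pre-vaccination sample, so only infection between samples matters.
- *By 6 months.* At the plan's implied 6% risk, 0.06 × 200 = 12 people. If an infected person's titre is k times higher, the GMT is multiplied by k^0.06: 4^0.06 = 1.09 and 16^0.06 = 1.18. That is 0.12 to 0.24 of one twofold step. It is an upper end for that risk, because it places the whole wave between vaccination and the last sample and allows no waning. The fold-rise is assumed.
- *By 4 weeks.* Spread the 20% attack rate evenly over an assumed wave of W = 8 to 28 weeks: h = −ln(0.8)/W, and the infected share is 1 − exp(−4h(1 − VE)). At VE 70% this gives about 7 down to 2 of 200. With no protection at all in those four weeks, an outer bound, it gives about 21 down to 6.

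**The case against.** **A reader might infer that VE is biased downward**, because people who have had the illness would decline vaccination and gather in the comparator. The documents say nothing about uptake after infection. Section 4.1.2 also allows sampling weighted towards priority groups, whose earlier exposure may be higher or lower. The direction is unknown.

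**A reader might also build large falls in VE.** If 10% of the cohort were already infected and only half of them vaccinated, half of the unvaccinated would be immune (0.05/0.10) against 5.6% of the vaccinated (0.05/0.90), and VE would read 1 − 0.0567/0.10 = 43%. That applies a deliberate refusal rate to every earlier infection, including those nobody recognised. If instead 1% of the cohort knew of an infection and half of them were vaccinated, 5% of the unvaccinated and 0.56% of the vaccinated would be immune, and VE would be 1 − 0.0597/0.19 = 68.6%.

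**Part of the matter is handled or could be left to an analysis plan.** Section 11.3 allows for other confounders, the list in 7.1 is open-ended, consent covers register data on baseline conditions, and 8.1.1 collects positive tests. The weekly contact in 8.1 asks about previous as well as current symptoms. A first episode can also be read as the first during follow-up. This limits the size of the problem but does not remove it: 11.3 itself fixes time at risk by compliance, the register extracts are tied only to missed cases, and nothing says that the symptom query reaches back before entry.

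**On immunogenicity the objection largely stands.** The day-0 sample covers earlier infection. The 6-month sample is described as a measure of long-term immunity, not of vaccine effect alone. Applying the 20% attack rate to this cohort would give 4^0.20 = 1.32 to 16^0.20 = 1.74, but that is the rate for the unvaccinated, and these people are recruited because they intend vaccination. Removing samples after infection from the main result would also condition on vaccine failure. It could take out poor responders and so raise the GMT.

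**Conclusion.** The point holds as a gap in the definition of time at risk (11.3) and in baseline data collection (7.1). The absence of exclusion criteria is not itself at fault; it suits an observational cohort drawn from the campaign's target group.

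VE is biased only if the share already infected differs by vaccination status. With assumed contrasts of 5% against 10% in either direction, VE moves from 70% to 68.3% or 71.6%; with 5% against 20%, to 64.4% or 74.7%. The planned data would not show which applies. Equal shares leave 70%. All of this rests on assumed shares and full protection after infection.

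For immunogenicity the effect is small and concerns mainly the 6-month sample: at most about 9–18% on the GMT at the implied 6% risk and a 4- to 16-fold rise, in a descriptive secondary analysis.

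**What to change.** - **11.3:** count time at risk only for people with no positive A(H1N1)v test before entry, using the laboratory and Communicable Disease Register extracts already planned in 8.1.1, with the search extended back before enrolment.
- **7.1:** add one baseline question on febrile respiratory illness since spring 2009, and name it in 11.3 among the confounders to be adjusted for. State its limits: it is not specific to A(H1N1)v, and subclinical infection is still missed.
- **8.2 and 11.3:** keep the all-samples fold-increase and GMT as the main result. Add a sensitivity analysis without samples taken after a confirmed A(H1N1)v infection.

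The cost is a few sentences and one question. The registers and ILI surveillance already cover these people, eligibility is unchanged, and the few people with an earlier positive test would contribute no time at risk. The question has to be in place before enrolment opens, since the history is hard to recover reliably afterwards.

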## **5 Definitions**

### **5.1 A(H1N1)v-influenza like illness (ILI)**

A(H1N1)v-influenza like illness (ILI) is defined as sudden onset of the following self-reported clinical signs and symptoms:

- fever ( $\geq 38^{\circ}\text{C}$ ) and at least one sign or symptom of acute respiratory infection or
- pneumonia diagnosed by a physician

## **5.2 Laboratory confirmation of influenza A(H1N1)v virus infections**

Cases of laboratory confirmed A(H1N1)v influenza are defined as events, where an individual belonging to the effectiveness and safety cohort and presenting with ILI defined in chapter 5.1. has A(H1N1)v influenza virus identified from a combined nasal and throat swab specimen obtained within five days after onset of the symptoms by methods described in chapter 10.2.1

- at least a 4-fold increase in A(H1N1)v influenza-specific antibody titers in serum specimens between the acute phase (0 to 5 days after onset of the symptoms) and convalescent phase (2-3 weeks after the acute phase serum sample) serum specimens will be used as additional information, if the person is unvaccinated or if at least 4 weeks have elapsed since receiving the last dose of A(H1N1)v vaccine at time of the acute phase sampling, but this is not a criteria for defining cases of laboratory confirmed influenza.

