## **5.3 Vaccinated persons**

The individual is defined as vaccinated if he/she has received at least one dose of A(H1N1)v vaccine, irrespective how much time has elapsed since the vaccination.

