## **6 Vaccinations**

It is anticipated that an A(H1N1)v vaccination campaign is conducted in the study area during the study period. The study subjects represent the target population of such a vaccination campaign and will thereby be offered at least one dose of A(H1N1)v vaccine during the study period by Tampere health centre. An agreement will be made with the health centre on recording the vaccinations individually in the electronic medical records of the health centre or into another database even during mass vaccinations.

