## **8 Study outcome assessment**

### **8.1 Assessment of effectiveness**

At enrolment, all 4,000 subjects participating in the effectiveness and safety cohort will be instructed to detect signs of ILI, defined in chapter 5.1. If ILI is present, the participants are instructed to contact the study staff immediately to have nasal and throat swab specimens and a blood sample taken as soon as possible, preferably within 3 days and at least within 5 days after the start of symptoms. Subjects are asked to fill in a diary in case of ILI to characterize the start of symptoms and clinical features of the disease. In addition, all study subjects will be contacted weekly by SMS, if possible, or by email or phone call in order to query any current or previous symptoms of ILI.

In case of ILI, an acute phase visit will be arranged 0 to 5 days after the onset of symptoms, either at the home of the subject or in the premises of collaborating health care settings or at a special study clinic established for the study. Nasal and throat swabs will be obtained by a qualified study nurse or physician, to define the cases of laboratory confirmed A(H1N1)v influenza (5.2). In addition, 10 ml of venous blood will be drawn at the acute phase. Clinical features of ILI will be recorded using the diary as an aid and a convalescent visit will be scheduled 2-3 weeks after the acute phase visit. Another diary will be given for follow up of the course of the disease. At the convalescent visit, 10 ml of venous blood will be drawn for measurement of the increase in A(H1N1)v virus specific antibody levels, and further information of the disease will be collected using the diary as an aid. After the first occurrence of laboratory-confirmed A(H1N1)v influenza case, no subsequent individual follow-up will be performed for the effectiveness outcome, i.e. for ILI.

The information regarding A(H1N1)v vaccination will be obtained from the health care data system of Tampere health centre.

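### Section 5.2 sets no condition on an A(H1N1)v dose given between the acute and convalescent sera, so a vaccine-induced rise could be taken as supporting infection

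*Protocol*

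**What the plan says.** **Serology.** Section 5.2 of the protocol defines a laboratory-confirmed case by virus found in a swab. It adds that a 4-fold rise between acute and convalescent serum serves as additional information on infection, "if the person is unvaccinated or if at least 4 weeks" lie between dose and serum. The time point of that test is the first serum: the 4 weeks must "have elapsed since receiving the last dose of A(H1N1)v vaccine at time of the acute phase sampling". The second serum belongs to the "convalescent phase (2-3 weeks after the acute phase serum sample"), and section 8.1 agrees: "a convalescent visit will be scheduled 2-3 weeks after the acute phase visit". Section 5.2 also limits the role of the rise: "this is not a criteria for defining cases of laboratory confirmed influenza".

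**Vaccination during follow-up.** Section 5.3 counts a person as vaccinated after one dose, "irrespective how much time has elapsed since the vaccination". Under section 6 participants "will thereby be offered at least one dose of A(H1N1)v vaccine during the study period". Section 1 says a second dose is under negotiation, and section 8.2 provides for one.

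**Immunogenicity.** Section 8.2, which section 11.1 makes the endpoint definition, says: "Immunogenicity will be assessed as the fold-increase between pre- and post-vaccination immune responses". Sampling is before vaccination, at 4 weeks, and at 6 months after the last dose for the long-term level. The section does not mention infection between samples.

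**The concern.** The 4-week condition has an evident purpose: to keep antibody rises caused by a recent dose out of the evidence for infection. A rise, however, is a difference between two sera, and a dose given after the first can produce it as well as a dose shortly before. The rule protects the start of the interval and leaves the interval itself open, at a time when the protocol expects a vaccination campaign. In a swab-negative illness, a vaccine response could then be put down as a sign of missed A(H1N1)v infection.

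Section 8.2 has the same problem in reverse. An infection between two samples of a vaccinated subject raises the later titre, and nothing in the definition separates that rise from the response to the vaccine.

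At stake are the supporting evidence on infection and the descriptive immunogenicity results.

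**Working it through.** **1. The plan's own figure.** Inputs from section 11.2: N = 4,000, 90% uptake, 20% attack rate in the unvaccinated, 70% effectiveness, lower 95% limit to exceed 50%.
- Unvaccinated: 400 × 0.20 = 80 cases.
- Vaccinated: 3,600 × 0.20 × 0.30 = 3,600 × 0.06 = 216 cases. Total 296.
- Expected share of cases who are vaccinated: 0.27/(0.27 + 0.10) = 0.730 at a relative risk of 0.30, and 0.45/(0.45 + 0.10) = 0.818 at 0.50.
- Exact binomial on 296 cases: the limit clears 50% when at most 228 cases are vaccinated, which has probability 95.1%.

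The stated 95% reproduces. Serology enters none of these steps, so changing the serology rule changes neither N nor power.

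**2. Who passes the rule in 5.2.**
- Dose less than 4 weeks before the acute sample: excluded, as intended.
- First dose at least 4 weeks before the acute sample, second dose before the convalescent sample: passes, because the 4-week test is applied at the acute sample.
- First dose between the two samples: passes if *unvaccinated* is judged at the acute sample. If it is judged when the pair is read, the person is vaccinated under 5.3, was not 4 weeks past a dose at the acute sample, and fails. The text gives *unvaccinated* no time point.

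**3. How often a first dose could fall in the gap (illustration).** Assumptions not in the protocol: doses and illness are both spread evenly over the same campaign of W weeks. From the protocol: 90% uptake and a gap of c = 2 or 3 weeks.
- Average share unvaccinated at the acute sample: 1 − 0.9/2 = 0.55.
- Average share dosed within the gap: 0.9 × c × (W − c/2)/W².
- Share of acute-unvaccinated pairs with a dose in the gap: 0.9 × c × (W − c/2)/(0.55 × W²).

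| W (weeks) | c = 2 | c = 3 |
|---|---|---|
| 8 | 12.6/35.2 = 36% | 17.55/35.2 = 50% |
| 16 | 27/140.8 = 19% | 39.15/140.8 = 28% |
| 26 | 45/371.8 = 12% | 66.15/371.8 = 18% |

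These are shares of pairs containing a dose. Not every such dose would give a 4-fold rise by the second sample, so for each W they bound the false rises from above. A campaign shorter than 8 weeks would give larger shares. Illness after the campaign contributes nothing. Second doses are not included, because no two-dose schedule is fixed.

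**4. Immunogenicity (illustration).** Assumption not in the protocol: infection multiplies the titre by 8. If a fraction q of subjects is infected before the sample, the geometric mean titre is multiplied by 8^q.
- 6-month sample, with the whole wave between vaccination and sampling: q = 0.20 × 0.30 = 0.06, or 200 × 0.06 = 12 subjects. 8^0.06 = 1.13, or 13% too high.
- 4-week sample, with a 20% attack rate spread evenly over T weeks and 70% protection: 200 × (1 − 0.8^(4/T)) × 0.30. T = 12 gives 4.3 subjects and T = 30 gives 1.8, so about 2-4 of 200 (q about 0.01-0.02). 8^0.01 = 1.02 and 8^0.02 = 1.04, or 2-4% too high.

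**The case against.** A reader might infer that swab-negative illnesses will be counted as cases and incidence inflated. The documents do not support that. Section 5.2 says the rise does not define a case, section 11.3 calculates incidence from laboratory-confirmed cases, section 10.2.2 presents the sera as additional information, and no serological incidence is planned. This part of the objection stands in full and limits the point to supporting evidence.

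It can also be said that 5.2 read together with 5.3 already excludes a first dose in the gap. That reading is possible, so it would be wrong to say that the rule plainly admits such a dose. It does not remove the problem: the sentence permits the opposite reading, and a second dose in the gap passes on either. The second-dose route does depend on a strategy not yet decided.

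The campaign length is an assumption. Section 1 expects early doses for only parts of the population, and section 15 lets follow-up run to 30 April 2010. The 12-50% is therefore an illustration.

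On immunogenicity, section 11.3 plans only a descriptive analysis, and the handling of infected subjects may stand in an analysis plan not shown. The 6-month sample is described as a measure of long-term level, not of vaccine response alone. A reader might infer a substantial bias throughout, but the 13% cannot apply to the 4-week result unless the whole wave falls within those 4 weeks. These objections make the immunogenicity half secondary. They do not remove it, since 8.2 defines the endpoint and infection would raise the level measured.

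**Conclusion.** The point holds as a minor flaw in a rule that the protocol states. Section 5.2 guards against a dose before the acute sample but not against one before the convalescent sample. A second dose in the gap passes outright, and a first dose passes on one of two readings. With even spread of doses and illness over an assumed 8-26 weeks, about 12-50% of pairs from persons unvaccinated at the acute sample would contain a dose, which is an upper bound on false rises within each assumed campaign length. The primary endpoint, the 4,000 participants and the 95% power are untouched.

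The immunogenicity point is secondary. On the plan's own inputs about 12 of 200 vaccinees would be infected over the wave. With an assumed 8-fold rise and the whole wave before the 6-month sample, the geometric mean titre there would be about 13% too high. At 4 weeks the effect is about 2-4%.

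**What to change.** **Section 5.2.** Use the 4-fold rise only if no A(H1N1)v dose was given from 4 weeks before the acute sample until the convalescent sample. This also settles when *unvaccinated* is judged. Vaccination records are already to be obtained (sections 6 and 8.1), so nothing new is collected. The cost is the loss, as supporting evidence, of serum pairs with a dose in the gap, which cannot separate vaccine response from infection anyway. No endpoint loses data.

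**Sections 8.2 and 11.3.** Show the descriptive immunogenicity results with and without samples taken after a positive A(H1N1)v test in that subject. Immunogenicity subjects belong to the total cohort, so their swab results are already available, and the cost is one extra display. Two limits should be stated beside it. Infections without influenza-like illness are not swabbed and stay in both sets. If weak responders are more likely to be infected, removing their later samples selects good responders, which is why a paired display is preferable to compulsory exclusion from the main analysis.
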